For patients with TGA (Transposition of Great Arteries) or HLHS (Hypoplastic Left Heart Syndrome), later cardiac surgery leads to a higher incidence of white matter injuries (WMI) (7, 8), which is a well-known prognostic factor for motor (9–12), language (11), and cognitive (10, 12, 13) impairment, as well as behavioral issues (14). Additionally, Anderson et al. (15) demonstrated that conducting the arterial switch operation (ASO) on neonates with TGA before the third day of life reduced the major postoperative morbidity of these patients in terms of neurological (occurrence of seizures, ischemic stroke), cardiological, and infection complications. Patients with left ventricle hypoplasia operated on later in the neonatal period also presented higher postoperative morbidity (16). Similarly, patients with TGA given the ASO after 2 weeks of life experienced impaired perioperative brain growth and slowed language development (17). Conversely, a major hypotrophy (weight < third percentile) or hemodynamic instability can delay the surgery, which may then be considered too risky. The fetal, pre and intraoperative risk factors of brain injuries are listed in the Table 1. All postoperative morbidities (Table 2) are deemed as potential risk factors for brain injuries.

**Table 1 T1:** Foetal and preoperative risk factors of brain injuries.

	Foetal period	Preoperative period	Intraoperative period
Risk Factors of Brain injuries	Gestational Age	Postnatal diagnosis	CPB duration (min)
	IUGR	Lower arterial oxygen saturation	Aortic clamp time (min)
	Brain volume	Lower apgar scores at 5 min	DHCA (min)
			Selective cerebral perfusion (min)
	Brain immaturity	Abnormal aEEG background pattern	Low Flow
		Longer time to surgery	
		Brain lactates	
		Low flow	
		Male sex	

CPB, Cardiopulmonary bypass; DHCA, Deep hypothermia with circulatory arrest; IUGR, Intrauterine growth restriction; aEEG, amplitude EEG.

**Table 2 T2:** Classification of post-op morbidities.

Morbidity category	Morbidities	
Cardiac / Respiratory	• Cardiac arrest, arrhythmias, JET • Low cardiac output syndrom • Extracorporeal membrane oxygenation • Post-op high-output failure • Re-intubation for acute respiratory distress	• Neonatal necrotizing enterocolitis • Systemic vein thrombosis • Acute renal deficiency with dialysis • Delayed sternal closure • Length of intensive care unit stay
Infectious	• Septicemia, fungemia • Infection of the surgical site, mediastinitis • Endocarditis	• Meningitis • Pneumonia

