Neurological	• Ischemic cerebrovascular accident • Hemorrhagic cerebrovascular accident	• Epileptic seizure • Cerebral thrombophlebitis
Surgical	• Recurring diaphragmatic paralysis/paresis • Definitive AV block with device • Acute hemorrhaging requiring revision surgery	• Cardiac tamponade • Unplanned revision surgery • Chylothorax

There is no consensus regarding the optimal age for surgery in terms of morbidity and neurodevelopmental outcomes, and its definition is a real challenge. Importantly, at the present time, there are no established rules for determining the timing of surgery in our department. For the most common CHD types, the TGA are corrected during the first ten days of life. There is a more pronounced degree of variation for HLHS. This common practice won't be changed for our observational study.

Our aim is to determine the relationship between surgical timing and long-term neurodevelopmental outcomes for various types of complex CHD. Similarly to Anderson et al. (15) with postoperative morbidity, we aim to determine a cut-off point for surgical timing that will improve neurodevelopmental outcomes. For each type of CHD, we aim to determine a cut-off for surgical timing based on postoperative morbidity and neurodevelopmental outcomes. We hope that our findings will contribute to the development of surgical timing guidelines in the future.

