#### Sample size

3.1.1.

Two previously published studies that reported a significant correlation between age at surgery and the incidence of WMIs included 26 and 37 patients, respectively (7, 8). Based on the active file of patients with complex CHD operated on each year in Cardiac Surgery at the La Timone Enfants Hospital, the total number of subjects included will be 100. With this number of 100 included patients and according to the values of (i) a 5% bilateral alpha risk and (ii) 80% statistical power, we estimate the minimum correlation coefficient between age at surgery and Bayley-IV test scores as 0.39.

According to the same hypotheses (5% bilateral alpha risk and 80% statistical power), and based on the intended number of patients recruited for each (Clancy) CHD subtypes, the minimum correlation coefficient that could be highlighted between age at surgery and Bayley-IV test scores is:
*r* = 0.38 for class I, two-ventricle heart without arch obstruction (*n* = 50)*r *= 0.65 for class II, two-ventricle heart with arch obstruction (*n* = 15)*r* = 0.76 for class III, single ventricle heart without arch obstruction (*n* = 10)*r* = 0.53 for class IV, single ventricle heart with arch obstruction (*n* = 25)”

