#### Main analysis

3.1.2.

The analysis of the main objective will be based on the evaluation of the correlation between the age at surgery (in number of days of life) and the main analysis criteria selected, namely the neurodevelopmental outcomes at 24 months assessed using the scores obtained on the Bayley-IV scale. The analysis will be conducted for the entire cohort and separately for each type of complex CHD to define the optimal age for surgery for each complex CHD type. To do this, Pearson's correlation coefficient will be estimated with a 95% confidence interval if the application conditions are met (otherwise, the non-parametric Spearman's rank correlation coefficient will be estimated with a confidence interval of 95%). A ROC curve will be plotted to curve to determine (according to Youden's method) the optimal threshold for the age at surgery that discriminates delayed neurodevelopment / normal neurodevelopment according to the main criterion, i.e. neurodevelopment at 24 months according to the Bayley-IV scale. The first secondary endpoint based on the AIMS scores at 4 months and 12 months will be analyzed using the same previously described strategy. The next secondary endpoint based on the clinical assessment by the child neurologist (neurodevelopment considered normal vs. abnormal) at 4 months, 12 months, and 24 months will be analyzed using a comparison test for quantitative data. A Student's t-test will be used if the application conditions are met; otherwise, the non-parametric Mann-Whitney test will be used.

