##### Moderating role of demographic and surgical factors

3.1.3.4.

The moderating role of demographic characteristics and pre-, intra-, and postoperative factors on the correlation between age at surgery (in number of days of life) and the various prognostic criteria for neonates with complex CHD indicated above will be analyzed using multivariate analyses. For quantitative data (neuropsychological development assessed using Bayley-IV scale scores, neurodevelopment assessed using AIMS scores, and length of postoperative hospitalization), a multivariate linear regression model will be employed. Each of the criteria previously listed will, in turn, be considered a dependent variable. Age at surgery, the explanatory variable of interest, will be systematically incorporated into the models. The main prognostic factors identified in advance according to an analysis of data from the literature, will also be incorporated into the models. Adjusted beta coefficients will be estimated with a 95% confidence interval. Standardized beta coefficients will also be presented to assess the relative role of each factor in the prognosis.

For qualitative data (neurodevelopment judged as normal vs. abnormal in the neuropediatric clinical assessment, the presence of WMIs, the element of morbidity), a multivariate logistics regression model will be utilized. Each of the criteria previously listed will, in turn, be considered a dependent variable. Age at surgery, the explanatory variable of interest, will be systematically incorporated into the models. The main prognostic factors identified in advance according to an analysis of data from the literature will also be incorporated into the models. Adjusted odds ratios will be estimated with a 95% confidence interval. In order to consider the small sample size, the Firth correction may be applied.

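### The main age-at-surgery analyses and the derived cut-off are unadjusted, although the protocol says timing varies with CHD type and clinical state; the adjusted regression is only secondary

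*Protocol article*

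**What the plan says.** Section 3.1.2 (Main analysis) fixes the method: "Pearson's correlation coefficient will be estimated with a 95% confidence interval if the application conditions are met", with Spearman's coefficient as the fallback. On scope it says "The analysis will be conducted for the entire cohort and separately for each type of complex CHD". An ROC curve with Youden's method is then used to find "the optimal threshold for the age at surgery that discriminates delayed neurodevelopment / normal neurodevelopment". No covariate enters the correlation or the ROC curve.

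The Introduction gives two reasons why age at surgery is not independent of prognosis:

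- On diagnosis: "the TGA are corrected during the first ten days of life. There is a more pronounced degree of variation for HLHS".
- On clinical state: "a major hypotrophy (weight < third percentile) or hemodynamic instability can delay the surgery".

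An adjusted analysis does exist. Section 3.1.3.4, under Secondary analysis, plans a multivariable linear regression of Bayley-IV score: "Age at surgery, the explanatory variable of interest, will be systematically incorporated into the models", together with prognostic factors taken from the literature. The article presents it as a study of moderating factors and does not name CHD type among the covariates. Type of CHD is among the data collected (section 2.9).

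**The concern.** A correlation over the whole cohort combines two things: the association between timing and score within a diagnosis, and any difference between diagnoses in both usual timing and usual score. Only the first bears on the study's question. If classes differ on both, the pooled coefficient can be non-zero with no timing effect in any class, or can hide a real one.

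Clinical state is a separate route. If infants who are small or unstable are operated on later and also score lower, later surgery will look harmful within every class. Splitting by CHD type does not remove this. A Youden cut-off on age alone inherits both problems.

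The stakes come from the intended use. The Discussion seeks a general optimal age as well as one per CHD type. The Conclusion looks ahead to timing guidelines and to an interventional study that reduces age at surgery.

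**Working it through.** **Inputs from the protocol article.** Sample size: "the total number of subjects included will be 100". Error rates: "a 5% bilateral alpha risk and (ii) 80% statistical power". Clancy classes I/II/III/IV of 50/15/10/25 (section 3.1.1). Bayley-IV SD 15 (section 2.8.2). No class means for age or score are given, so the class gaps below are assumptions.

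**1. The plan's own figures.** The detectable correlation is r = tanh[(1.960 + 0.842)/√(n − 3)].

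| n | Stated r | Computed r |
|---|---|---|
| 50 | 0.38 | 0.387 |
| 15 | 0.65 | 0.669 |
| 10 | 0.76 | 0.785 |
| 25 | 0.53 | 0.535 |
| 100 | 0.39 | 0.277 |

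The class figures agree with the stated inputs (0.384, 0.657, 0.770 and 0.528 with a small-sample correction). The whole-cohort 0.39 does not: it corresponds to n = (2.802/0.412)² + 3 ≈ 49. That is a separate matter and does not decide this point. The reference value used here is 0.277.

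**2. Pooled correlation with no timing effect in any class.** Assume that single-ventricle classes III and IV (35%) differ from two-ventricle classes I and II (65%) by g within-class SDs of age and by b Bayley points. With p(1 − p) = 0.65 × 0.35 = 0.2275:

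r = −0.2275·g·b / √[(1 + 0.2275g²)(225 + 0.2275b²)]

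Rejection rate ≈ Φ(atanh|r|·√97 − 1.96).

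| g (SD) | b (points) | Pooled absolute r | Rejection |
|---|---|---|---|
| 0.5 | 5 | 0.036 | 5% |
| 1.0 | 10 | 0.130 | 25% |
| 1.0 | 15 | 0.185 | 45% |
| 1.5 | 15 | 0.250 | 71% |

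For g = 1, b = 10: 2.275/√(1.2275 × 247.75) = 2.275/17.44 = 0.130. The rejection formula counts only the tail in the direction of r. In the first row, adding the other tail gives 0.055 + 0.010 = 6.5%, so the low end is close to nominal. The sign of r depends on which group is operated on later.

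**3. Distortion of a real effect.** Let the true within-class r be −0.28, which adds −0.28 × 15 = −4.2 to the covariance.

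- g = 1, b = 10: pooled r = (−2.275 − 4.2)/17.44 = −0.37 if the lower-scoring group is operated on later, and (2.275 − 4.2)/17.44 = −0.11 if earlier.
- g = 1.5, b = 15: −0.46 if later, +0.04 if earlier.

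**4. Clinical state within a class.** If a severity factor correlates a with age at surgery and a in the opposite direction with score, the spurious correlation has size a². For a = 0.3, 0.4 and 0.5 (assumed) it is 0.09, 0.16 and 0.25. In class I (n = 50) the rejection rates are about 9%, 20% and 42%.

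**5. Cost of adjusting.** With k covariates, replace n − 3 by n − 3 − k.

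- Class only (k = 3): tanh(2.802/√94) = 0.281.
- Class plus eight covariates (k = 11): tanh(2.802/√86) = 0.293.

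**The case against.** The best defence is that the plan already holds most of the remedy. The main analysis is not only pooled: it is repeated by CHD type, with the stated purpose of an optimal age per type, and section 3.1.1 gives a detectable correlation for each class. That removes much of the confounding by diagnosis, and it stands. Its limits are that classes II and III can detect only correlations of 0.65 and 0.76 on the plan's own figures, that class I still groups TGA with tetralogy of Fallot, truncus arteriosus and TAPVR, and that stratifying by type leaves clinical state untouched.

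The adjusted regression is also planned, so the dispute is about its rank. That stands too, and it is why the change is small. A covariate list can properly be left to an analysis plan that is not shown here.

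The non-inclusion criteria (birth weight under 2 kg, gestation under 37 weeks, proven genetic syndrome) narrow some confounding. They do not address hemodynamic instability. The Limitation section calls the work preliminary and mentions heterogeneity, but not confounding.

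A reader might infer more: that diagnosis dictates timing, that single-ventricle infants are operated on later and fare worse, or that the pooled test would be falsely positive in about half of cohorts. The documents support none of these. They report no established timing rules, a window for TGA, wider variation for HLHS and a possible delay for small or unstable infants. They give no mean age or score by class.

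**Conclusion.** The point holds in a limited form. The correlations and the Youden cut-off carry no covariates, while the protocol itself links age at surgery to CHD type and to clinical state. The pooled estimate mixes diagnosis with timing. Confounding by clinical state remains in the pooled and by-type correlations and in the cut-off, and the estimate that addresses it is ranked secondary.

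Neither the size nor the direction of the bias can be derived from the documents. The range of about 5–71% false rejection rests on assumed gaps of 0.5–1.5 SD in age and 5–15 Bayley points between single- and two-ventricle classes. The spurious 0.09–0.25 within a class rests on assumed correlations of 0.3–0.5. These figures show that the bias could run from negligible to decisive; they do not predict it. This is an inexpensive improvement to settle before analysis, not evidence that the study cannot answer its question.

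**What to change.** - Make the main whole-cohort estimate the linear regression already described in section 3.1.3.4: Bayley-IV score on age at surgery, adjusted for Clancy class and a short pre-specified list of collected preoperative variables (for example birth weight, prenatal diagnosis, preoperative ventilation or cardiac arrest, and parental education).
- Leave postoperative variables out of this model, as they may lie on the path from timing to outcome. For the same reason avoid covariates that grow with waiting time, such as days of preoperative ventilation.
- Report the slope in Bayley points per day with its 95% confidence interval.
- Keep the by-type analyses in the main analysis, adjusted where numbers allow or obtained through an age-by-class interaction, so that a common slope is not imposed on all classes.
- Label the crude pooled correlation and the unadjusted ROC/Youden cut-off as descriptive.

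Cost: no new data, since these variables are listed in section 2.9, and a few degrees of freedom (detectable correlation 0.281–0.293 against 0.277). Section 3.1.1 needs matching wording, and its whole-cohort figure should be rechecked at the same time.

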## Conclusion

6.

We will conduct a preliminary observational study to determine the most appropriate surgical timing for each type of complex CHD. This project aims to determine whether an earlier surgery would be a beneficial neuroprotective strategy to reduce brain injuries and postoperative morbidities and improve neurodevelopmental outcomes. This research should be useful in developing guidelines for optimal surgical timing for complex CHDs in the near future. Based on the balance between benefit and risk, these guidelines will make it easier to determine the optimal surgical timing for a newborn or infant with a complex CHD. Secondly we will conduct an interventional study to reduc the age at surgery.

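### An optimal age per CHD type is derived from separate small-group analyses, with no stated comparison between types and no interval for the cut-offs

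*Protocol article*

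**What the plan says.** Under Main analysis (3.1.2), the relation between age at surgery and the 24-month Bayley-IV scores is estimated by Pearson or Spearman correlation with a 95% confidence interval: "The analysis will be conducted for the entire cohort and separately for each type of complex CHD to define the optimal age for surgery". A ROC curve with Youden's method then gives "the optimal threshold for the age at surgery that discriminates delayed neurodevelopment / normal neurodevelopment according to the main criterion". Section 1.2 sets the split at a score of 80. No interval is stated for this cut-off.

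Type-specific timing is an aim in its own right. The Introduction says "For each type of CHD, we aim to determine a cut-off for surgical timing based on postoperative morbidity and neurodevelopmental outcomes", and the Conclusion (section 6) says the study will "determine the most appropriate surgical timing for each type of complex CHD" and expects the results to inform guidelines.

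Section 3.1.1 plans "the total number of subjects included will be 100" and lists a detectable correlation for each Clancy class at "5% bilateral alpha risk and 80% statistical power". It gives 0.38 "for class I, two-ventricle heart without arch obstruction" (n = 50), 0.65 for class II (n = 15), 0.76 "for class III, single ventricle heart without arch obstruction" (n = 10) and 0.53 for class IV (n = 25).

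Section 3.1.3.4 adds whole-cohort multivariable regressions under a moderator heading. Age at surgery is always included, and the stated outputs are adjusted betas and odds ratios. Section 2.9 lists CHD type among the preoperative data, but 3.1.3.4 names neither CHD type nor an age-by-type term.

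**The concern.** Four separate estimates from groups this small will scatter widely. If they are set side by side as the optimal age for each type, a reader will take the differences as real. The plan states nothing that would tell a genuine difference in timing from sampling variation: no between-type contrast, and no measure of uncertainty on the quantity of interest, the cut-off in days. The study could therefore support different timing for different lesions when its data are compatible with one common relation. That matters because the stated purpose is to inform timing guidelines by type.

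**Working it through.** **1. The article's class figures reproduce.** Method: Fisher z with a t-based critical r and bias term r/(2(n-1)), two-sided 5%. Power at the stated values:

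- n = 50, r = 0.38: 0.790
- n = 15, r = 0.65: 0.788
- n = 10, r = 0.76: 0.782
- n = 25, r = 0.53: 0.804

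All lie within two points of 0.80, so the class sizes are a sound basis for what follows. The whole-cohort figure of 0.39 does not reproduce (0.276 at n = 100). That is a separate matter and is not used here.

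**2. Precision within a class.** The interval is tanh(atanh(r) ± 1.96/√(n-3)). For an observed r of -0.30:

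- n = 50: -0.53 to -0.02
- n = 15: -0.70 to 0.25
- n = 10: -0.78 to 0.41
- n = 25: -0.62 to 0.11

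**3. Discordant significance under one common relation.** Assume the same true r in every class. P(some but not all classes significant) = 1 - Π(power) - Π(1 - power). At r = -0.30 the powers are 0.572, 0.196, 0.136 and 0.314:

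- Π(power) = 0.572 × 0.196 × 0.136 × 0.314 = 0.005
- Π(1 - power) = 0.428 × 0.804 × 0.864 × 0.686 = 0.204
- Result: 1 - 0.005 - 0.204 = 0.79

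The same formula gives 0.51 at -0.20 and 0.93 at -0.40. In simulation at -0.30, the median gap between the highest and lowest class r is 0.44, and about 35% of studies have at least one class with the opposite sign.

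**4. Spread of the cut-offs in days under one common relation.** The article gives no distribution of age at surgery and no expected Bayley distribution for this cohort, so these are assumptions. 5,000 trials per scenario were simulated, with one Youden cut-off per class for Bayley below 80.

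- Wide age spread (median 10 days, log-SD 0.8, limited to 1 to 60 days; Bayley mean 85 to 100, SD 15; r from 0 to -0.39): the four cut-offs span a median of 11 to 17 days, and at least 5 days in 86 to 95% of trials.
- Tight age spread (median 7 days, log-SD 0.5, Bayley mean 90, r = -0.30): the median span is about 5 days.
- With a Bayley mean of 100, the class III cut-off cannot be computed in about 38 to 40% of trials. At a mean of 85 this is about 1%.

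For scale, the Introduction says that TGA is corrected within the first ten days of life.

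**5. What a between-class test could show.** Take Q = Σ(n-3)(z - z̄)² on 3 df, where z is the Fisher-transformed class correlation and z̄ its weighted mean. The weights n - 3 are 47, 12, 7 and 22 (sum 88). For true r of -0.39, 0, 0 and -0.39 in classes I to IV, z is -0.412 in classes I and IV:

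- z̄ = -0.412 × 69/88 = -0.323
- Noncentrality = 69 × 0.089² + 19 × 0.323² = 0.55 + 1.98 = 2.5
- Power: about 0.24

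For -0.5, -0.2, -0.2 and 0 the power is about 0.44. For -0.6, 0, 0 and 0 it is about 0.78.

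**The case against.** **The plan does contain a joint model.** A reader might infer that it has none. That is true of 3.1.2 only. Section 3.1.3.4 fits whole-cohort regressions of Bayley-IV score with age always included and a stated moderator aim, and CHD type is among the data collected. This limits the point but does not remove it: as described, the outputs are main effects, no age-by-type term is named, and nothing links these models to the type-specific ages.

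**The article acknowledges imprecision.** It plans confidence intervals for the correlations, discloses that detectable correlations rise to 0.65 and 0.76 in the small classes, concedes in section 5 that timing may be definable only for frequently recruited lesions, and calls the work preliminary. It nowhere says that significance in one type and not in another will be read as a difference. This is fair, but the concession changes no analysis, and the Conclusion still promises a timing for every type.

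**An article condenses the full protocol.** A heterogeneity test or interval method may be specified elsewhere, and its absence alone would be no finding. What the article does fix is that the analyses are separate and that their purpose is to define an age per type. That stated choice is the issue.

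**A joint model has limits.** A linear slope yields no optimal age and leaves the cut-offs as noisy as before. With four classes, the between-class variance needed for partial pooling is poorly estimated. Both objections stand, and the fix allows for them.

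**Conclusion.** The point holds in this form: an optimal age per CHD type is to be defined from separate correlations and Youden cut-offs in about 50, 15, 10 and 25 infants, with no stated between-type comparison and no interval for the cut-offs. Under one common relation, discordant significance would arise in about 79% of studies at r = -0.30 (51% at -0.20, 93% at -0.40), and the cut-offs would differ by about 5 to 17 days.

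The discordance figures rest on the article's class sizes and an assumed common r. The spans in days also depend on the assumed age and Bayley distributions and should be read as orders of magnitude. If type means the finer diagnoses of Table 3 rather than the Clancy classes, the groups are smaller and the scatter larger.

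A reader might go further and conclude that any observed differences will be due to noise alone. The documents do not support that, because true differences between lesions may exist. What is shown is that the cut-offs would differ even without them, and that the stated analysis could not tell the two situations apart.

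**What to change.** In 3.1.2, add one regression of Bayley-IV score on age at surgery with class-specific intercepts and an age-by-class interaction. Report the heterogeneity test, the common within-class slope, and each class's slope with its 95% confidence interval. Partial pooling of the slopes is optional, as a sensitivity analysis.

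Report each class's Youden cut-off with a bootstrap 95% confidence interval, and say where a cut-off cannot be computed. Keep the separate correlations and cut-offs as descriptive results. Do not claim that optimal timing differs between types unless the between-class comparison supports it, and bring the Conclusion into line with that rule.

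The cost is one model, a resampling step and some wording; no extra infants, visits or data are needed. The downside should be written into the plan: the heterogeneity test has low power at these class sizes (about 0.24 to 0.78 for the large contrasts shown above), so a non-significant result does not show that the types share one timing.

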## Discussion

4.

The correlation between surgical timing and long-term neurodevelopmental outcomes in children with complex CHD has not been fully studied. Moreover, currently, there is no consensus regarding the optimal surgical timing for neonates with complex CHD. Our study will allow us to define the optimal time-window within the neonatal period to perform cardiac surgery to reduce postoperative morbidity (i.e., postoperative complications) and optimize the neurodevelopment of infants with complex CHD. We hope our work will facilitate the evaluation of the risk/benefit ratio of the chosen therapeutic strategy.

A better understanding of the mechanisms underlying neurodevelopmental disorders in this population will allow the identification of other modifiable risk factors and the development of new prevention and screening strategies to improve the neurodevelopment and overall health of children and adults.

An added challenge for this field is the recruitment of patients with various types of CHD to define a general optimal age for cardiac surgery and an optimal age for each CHD type and not only for TGA and HLHS, which have been studied in more depth.

Moreover, the patients in our study will receive a neurodevelopmental follow-up at 4 months, 12 months, and 24 months. They will benefit from early screening for neurodevelopmental disorders with an orientation toward adapted rehabilitation structures, thereby supporting improvements in their overall neurodevelopmental outcome. The aim is to extend this treatment process to all patients with complex CHD who undergo surgery in their first weeks of life. This project, initially internal in hospitals in Marseille, could be extended with the collaboration of pediatric cardiology and neurology teams across France.

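### A correlation plus one cut-off can test whether earlier surgery is better, but cannot show or locate the optimal age or time-window that the protocol says it will define

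*Protocol article*

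**What the plan says.** Section 3.1.2 (Main analysis) relates age at surgery in days to the 24-month Bayley-IV scores, for the whole cohort and "separately for each type of complex CHD to define the optimal age for surgery for each complex CHD type". The method follows directly. For Pearson's measure, the text says that the "correlation coefficient will be estimated with a 95% confidence interval if the application conditions are met". Where those conditions fail, Spearman's coefficient takes its place, also with a 95% interval. A ROC curve with Youden's method then yields "the optimal threshold for the age at surgery that discriminates delayed neurodevelopment / normal neurodevelopment".

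The Discussion describes the deliverable more broadly: "Our study will allow us to define the optimal time-window within the neonatal period to perform cardiac surgery". The Conclusion speaks of the most appropriate timing for each type of heart disease, of guidelines, and of a later interventional study to lower the age at surgery.

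The Abstract and section 1.1 hypothesise that earlier surgery is better. Section 1.2 sets a correlation and a threshold (score below 80 against 80 or above) as the main objective, and the Introduction aims at a cut-off. For the Bayley-IV score, section 3.1.3.4 names a multivariate linear regression that contains age. No curved term in age is stated in either analysis section.

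**The concern.** Pearson's coefficient measures linear association and Spearman's measures monotone association. An optimum inside the observed range is neither: outcomes rise up to it and fall after it. A window has two edges, and a single Youden cut-off can return only one. The stated purpose (an optimal age, a window) therefore does not match the stated tools (a monotone coefficient and one split).

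If the relation were an inverted U, the coefficient would mostly reflect how the sampled ages lie around the optimum. It could be close to zero although timing matters, or it could be clearly negative or positive and give a one-directional message. The protocol intends its results to feed timing guidelines and a further trial, so either misreading would carry forward.

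**Working it through.** **The plan's own figure.** Section 3.1.1 gives 0.39 as the smallest detectable correlation for n = 100, two-sided 5% alpha and 80% power. The usual formula is tanh[(1.960 + 0.842)/√(n − 3)] = tanh(2.802/9.849) = 0.277, so 0.39 is not reproduced; it corresponds to n of about 49. That is a separate matter. Either figure describes sensitivity to a trend and says nothing about an optimum.

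**Inputs from the protocol.** n = 100 (3.1.1); Bayley SD 15 (2.8.2), used as the residual SD; surgery within 2 months of birth (2.1), taken as days 1–60.

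**Inputs assumed.** The article gives no age distribution and no expected curve. Age A is taken as log-normal with median 9 days and log-SD s from 0.6 to 1.0. The Bayley score is 100 − 4·[(ln A − ln m)/s]² + error, where m is the optimal age.

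**Why the coefficient depends on m.** Put U = (ln A − ln 9)/s and d = ln(m/9)/s. Ignoring the limits at days 1 and 60, U is standard normal. Then:

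- Cov(U, Y) = 8d
- Var(Y) = 16·(2 + 4d²) + 225 = 257 + 64d²
- correlation of the score with log-age = 8d/√(257 + 64d²)

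| Optimum m | s | d | Correlation |
|---|---|---|---|
| day 9 | any | 0 | 0 |
| day 5 | 0.6 | −0.980 | −7.84/17.84 = −0.44 |
| day 5 | 1.0 | −0.588 | −4.70/16.71 = −0.28 |
| day 14 | 0.6 | +0.736 | 5.89/17.08 = +0.34 |
| day 14 | 1.0 | +0.442 | 3.53/16.42 = +0.21 |

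The curvature is the same in every row. Only its position relative to the ages changes, and the sign changes with it.

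**Simulation of the same model with ages limited to 1–60 days, n = 100.** The 2-df test is regression on ln A and its square.

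| Optimum | Spearman | Pearson (days) rejects | 2-df test rejects |
|---|---|---|---|
| day 9 | near 0, rejects 6–7% | 13–24% | 58–87% |
| day 5 | −0.23 to −0.40 | | |
| day 14 | +0.21 to +0.32 | | |

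Ranges are over s = 0.6 to 1.0. Repeat runs move the percentages by one or two points. Pearson rejects more often than Spearman at day 9 because the long right tail of raw days pulls it slightly negative.

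**Other shapes (also assumed).**

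- Ages uniform on 1–60, optimum at day 30.5, 25 points lost at either end: Pearson and Spearman average 0.00 and reject in 6% and 7%; a test on age and its square rejects in 99%. The ROC step does not help: AUC is 0.50, and the Youden cut-off has median 49.5 days (interquartile range 46.1–52.7), on the late side only.
- The same with the optimum at day 20: Pearson −0.52, power about 100%. The trend is found, but the early edge is not.

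**The case against.** The strongest reply is that the test fits the hypothesis. The Abstract, section 1.1 and section 1.2 are about earlier being better and about a threshold, and a monotone coefficient with one cut-off serves those. The word window comes from the Discussion and could be read as operating by a certain day. This stands, and it is why the correlation should stay. It does not cover the text of section 3.1.2, which presents the correlation as the means of defining the optimal age by type, or the Discussion's promise.

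A reader might infer that a near-zero coefficient will be declared to mean that timing is irrelevant. The documents do not support that: the coefficient is to be estimated with a confidence interval, and no rule says how a null result will be read.

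A reader might also infer that a null is the expected outcome. It is not. It needs an optimum near the centre of the observed ages. With s = 0.6, moving the optimum from day 9 to day 6 raises Spearman's rejection rate from 7% to 86%. The error is then a one-directional reading rather than a false negative.

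Nor does the Introduction assert an inverted U. It says that low weight or "hemodynamic instability can delay the surgery, which may then be considered too risky", which describes sicker infants being operated on later. That is confounding by indication, not evidence that early surgery harms development.

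Finally, the form of a regression is often left to the analysis plan, which is not shown. That answers a complaint about missing detail. It does not answer a stated pairing of aim and method that cannot work.

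**Conclusion.** The point holds as a mismatch between aim and tool. As written, the main analysis can support or fail to support a monotone trend and can propose one cut-off. It cannot support a statement that an optimal age or a two-sided window exists, or where it lies.

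The size depends on an unknown curve. If the relation is monotone, nothing is lost. If it is an inverted U of the assumed strength centred on the median age, the rank correlation rejects barely more often than its 5% error rate, while a curved model rejects in more than half of trials. If the optimum lies to one side, the coefficient is clearly non-zero, but its sign reflects the ages sampled. Everything in these figures is assumed except n, the Bayley SD and the 2-month limit. The change is worth making but is not a fatal defect: the primary test remains valid for the hypothesis it was chosen for.

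**What to change.** 1. In section 3.1.2, keep the correlation and say that it tests whether earlier surgery is better.
2. Add one pre-stated model of the Bayley-IV score on log(age at surgery) and its square, or a 3-knot spline. Report a test of curvature and the fitted curve with its 95% band. Do this for the whole cohort and, as description only, for the larger classes (planned n = 50 and 25). Classes of 15 and 10 are too small for a useful curve.
3. State that an optimal age or window will be claimed only if that curve supports it. Otherwise, limit the conclusions in section 3.1.2 and the Discussion to a monotone trend and a cut-off.

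The cost is one extra model and no new data. Placed beside the correlation, it takes no power from it. Used instead of the correlation it would cost a little: under one assumed straight fall in log-age, Spearman had 77% power and the 2-df test 71%. The curve remains an association; it does not remove the confounding by indication noted above.
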